#### Participant timeline {13}

Children will be included after confirmation of the administration of vitamin A and the first dose of AQSP of the first SMC round. Eligible children will be followed-up for 1 year (Fig. 1). This will consist of an active surveillance system during the first 6 months to fully cover the malaria peak followed by a passive surveillance system for the rest of the period. During the active surveillance period, scheduled visits will be performed monthly. Anthropometric indicators and occurrence of adverse events will be recorded at each visit. Blood samples will be collected for microscopy slides, haemoglobin measurement, and spotted onto filter paper for further polymerase chain reaction (PCR) analyses.

**Table Tabb:** 

	Study period									
	Enrolment	Allocation	Post-allocation							
Timepoint**	− t_**1**_	0	M_**1**_	M2	M3	M4	M5	M6	M7–M11	M12 (Close-out)
**Enrolment**										
**Eligibility screen**	X									
**Informed consent**	X									
**Confirmation of SMC drug intake**		X								
**Confirmation of vitamin A intake**		X								
**Allocation**		X								
**Interventions**										
**[SMC + vitamin A + Plumpy’Doz]**			X	X	X	X				
**[SMC + vitamin A + zinc]**			X	X	X	X				
**[SMC + vitamin A]**			X	X	X	X				
**Assessments**										
**[Body temperature]**			X	X	X	X				X
**[Weight]**			X	X	X	X	X.	X		X
**[Height]**			X	X	X	X	X	X		X
**Malaria RDT**			X	X	X	X	X	X		X
**Malaria microscopy**			X	X	X	X	X	X		X
**MUAC**			X	X	X	X	X	X		X
**Haemoglobin measurement**			X	X	X	X	X	X		X
**Blood spots for PCR**			X	X	X	X	X	X		X
**Adverse events**			X	X	X	X	X	X		X

Axillary temperature will be determined using an electronic clinical thermometer. Mid-upper arm circumference (MUAC) will be measured at the mid-point between the tip of the shoulder and the tip of the elbow. Height will be measured using an appropriate Rolla-meter and recorded in centimetres. Weight will be measured using a baby scale for children aged 6 months to 2 years old, and a children’s sitting/standing scale for children over 2 years old. Blood will be collected by finger prick for haemoglobin (Hb) measurement, malaria Rapid Diagnostic Test (RDT), microscopy, and on filter paper for later PCR analyses. A HemoCue® 201^+^ will be used for photometric measurement of Hb in the field following the manufacturer’s procedure. Thick and thin blood films will be stained with Giemsa 3% for 30 min and examined with light microscope. A slide will be declared negative if the examination of 100 thick-film fields does not reveal the presence of asexual parasites. PCR analyses concern a genotyping of amodiaquine resistance molecular markers (*pfcrt* and *pfmdr1*), sulfadoxine resistance marker (*pfdhps*), and pyrimethamine resistance marker (*pfdhfr*) on malaria-positive samples [20]. Participant timeline can be summarized as follows:

#### Sample size {14}

Sample size calculation was carried out with incidence of malaria as the primary outcome measure under the assumption that the expected proportion of children 6–59 months who will acquire malaria in the absence of seasonal malaria chemoprevention (SMC) during the rainy season in Burkina Faso is 50%. The introduction of SMC is expected to reduce this proportion to 30%. The SMC programme together with nutritional intervention is expected to reduce this to 20%. The aim is to demonstrate that SMC + nutritional supplement arm is superior to the SMC alone arm in reducing the incidence of malaria. On this basis, a one-side α of 0.025 was chosen. Type II error was controlled at 20% (i.e. β = 0.20 or 80% power). Based on these parameters, a sample size of 294 was required for each pair-wise comparison (SMC + vitamin A vs SMC + vitamin A + zinc, and SMC + vitamin A vs SMC + vitamin A + Plumpy’Doz™). Hence, an overall sample size for the study was estimated at 882 (3 × 294) to detect a 10% difference in risk of malaria occurrence between SMC alone group and any of SMC + supplement group. Further assuming that 20% of the individuals will be lost to follow-up, an adjusted sample size of 353 children per arm was required. The final estimated sample size for this study is thus 1059 children.

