#### Plans to promote participant retention and complete follow-up {18b}

For studies with such a long follow-up period (12 months), loss to follow-up is an important issue. Therefore, by relying on Nanoro health and demographic surveillance system (HDSS), this risk is highly minimized. In addition, 20% corrective measure was allocated to this risk in the sample size calculation to prevent it from affecting the study validity. The supplements that will be used in this study (Plumpy’Doz and zinc) are well known by the population in the management of malnutrition. However, this study will insist on communication with the community/parent/guardians before enrolment in order to improve knowledge and awareness of study product as well as the purpose of the study.

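### The 353 children per arm said to be required under 20% loss is 294 × 1.2; it covers a loss of about 16.7%, and at 20% loss pairwise power is about 78.5% (minor)

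*Protocol article*

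**What the plan says.** The Protocol article, Sample size {14}, assumes that 30% of children acquire malaria with SMC and 20% with SMC plus a nutritional supplement. The design is "to detect a 10% difference in risk of malaria occurrence between SMC alone group and any of SMC + supplement group". On the error rates it says "On this basis, a one-side α of 0.025 was chosen", with power of 80%. From these inputs it obtains 294 per arm; the article's own product 3 × 294 = 882 confirms that 294 is a per-arm number.

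The allowance for attrition follows: "Further assuming that 20% of the individuals will be lost to follow-up, an adjusted sample size of 353 children per arm was required". The total is then given: "The final estimated sample size for this study is thus 1059 children".

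Plans to promote participant retention and complete follow-up {18b} refers back to this allowance, in the context of the 12-month follow-up: "20% corrective measure was allocated to this risk in the sample size calculation to prevent it from affecting the study validity". The inflation formula is not stated in either section.

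**The concern.** Sample size {14} defines the 20% as a share of the individuals in the study, so it applies to the number enrolled. The number to enrol is then the number needed divided by the fraction retained. Multiplying the number needed by 1.2 is a different calculation. It adds 20% of the smaller number, and a 20% loss from the larger number then takes away more than was added.

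The enrolment target of 1059 rests on this step. If the step is wrong, the article calls a number sufficient for 20% loss when, on its own inputs, it is not. Both comparisons with control are affected equally, because the same inflation is used for all three arms.

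**Working it through.** **Inputs**, all from Sample size {14}: p1 = 0.30, p2 = 0.20, one-sided α = 0.025 (z = 1.960), power 80% (z = 0.8416), loss d = 0.20. Allocation is 1:1:1 (Trial design {8}).

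**1. Reproduce the base number.** Pooled two-proportion formula without continuity correction, mean proportion 0.25:

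n = [1.960 × √(2 × 0.25 × 0.75) + 0.8416 × √(0.30 × 0.70 + 0.20 × 0.80)]² / 0.10²
= [1.960 × √0.375 + 0.8416 × √0.37]² / 0.01 = 293.15, so **294 per arm**. This matches the article.

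**2. Reproduce the adjusted number.**

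- n × (1 + d) = 294 × 1.20 = 352.8, so **353**. This matches the article, and 3 × 353 = 1059.
- n / (1 − d) = 294 / 0.80 = 367.5, so **368**, and 3 × 368 = 1104. This does not match.

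Other base formulas do not rescue 353 by division: the unpooled formula gives 291 and 291/0.8 = 364; the arcsine formula gives 292 and 292/0.8 = 365.

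**3. Children left after a 20% loss.** 353 × 0.80 = 282.4 per arm, about 12 below 294. In total, 1059 × 0.80 = 847.2, against 882 required.

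**4. Power at the retained number.** Power = Φ{[0.10 − 1.960 × √(0.375/n)] / √(0.37/n)}.

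- n = 294: (0.03000 / 0.03548) = 0.846, power **80.1%**.
- n = 282: (0.02853 / 0.03622) = 0.788, power **78.5%**.

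Exact enumeration of the pooled z-test gives 78.6% at 282 and 80.3% at 294; the unpooled approximation gives 78.8% at 282. The result does not depend on the approximation chosen.

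**5. The loss that 353 does cover.** 1 − 294/353 = 59/353 = **16.7%**.

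**6. Gap to the matching target.** 368 − 353 = 15 per arm; 1104 − 1059 = 45 in total.

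**The case against.** Four points can be made in the article's defence.

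*The effect is negligible.* A loss of about 1.5 power points is smaller than the uncertainty in the planning inputs. With 294 per arm, raising the assumed supplement-arm risk from 20.0% to 20.2% lowers power by about as much, to 78.4% by the same formula. This stands, and it fixes the severity as minor. It does not make 353 the right number for the stated loss.

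*A 20% add-on is a common convention.* The retention section speaks only of a 20% corrective measure, and an add-on of that size was in fact made. A reader might infer that this section promises full cover of a 20% loss with power held at 80%. It does not: it never mentions power, and its wording fits a plain add-on. The contradiction lies within Sample size {14}, which defines the 20% as individuals lost.

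*Not every lost child is lost to the outcome.* The calculation uses malaria during the rainy season, while the retention section ties the allowance to 12 months. According to Participant timeline {13}, the active surveillance of the first 6 months covers the malaria peak. A child lost later may already have supplied the outcome. This stands as a condition: 78.5% holds only if all 20% are unevaluable for that outcome. The article does not say when losses are expected.

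*Analysing person-time could recover information.* Perhaps in part, but the stated calculation is on proportions and takes no such credit.

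**Conclusion.** The point holds as a minor arithmetic error. On the article's own inputs, 353 per arm is not the number required under a 20% loss; 368 is. With 353, a 20% loss leaves about 282 per arm and pairwise power of about 78.5%, compared with the 80% used to derive 294. The power figure rests on three assumptions: the planning proportions of 30% and 20%, a test of two proportions at one-sided 0.025, and no outcome information from any lost child. If loss to the rainy-season outcome is 16.7% or less, 353 per arm is enough.

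A reader might go further and infer that the trial is materially underpowered or its validity threatened. The figures do not support that. The error does not bias the treatment comparison or change the type I error, and the precision achieved will be seen in the confidence intervals from the children actually retained.

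**What to change.** In Sample size {14}, replace the sentence on the adjusted number with wording such as: *With 353 children per arm (1059 in total), 80% power is kept for losses of up to about 16.7%; if 20% of children are unevaluable for the malaria outcome, power for each comparison with control is about 78.5%.* In Plans to promote participant retention {18b}, refer to that figure instead of to a 20% correction.

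No added enrolment is asked for. Trial status says that recruitment began on 13 July 2020 and was expected to take two weeks, so the matching target of 368 per arm (1104) serves to show the size of the slip. The cost is one sentence, a cross-reference and a slightly less favourable stated figure.

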#### Recruitment {15}

The study will rely on existing Health and Demographic Surveillance System (HDSS) for identification of eligible participants. All the participants will be recruited within the coverage area of the Nanoro HDSS.

#### Assignment of interventions: allocation

##### Sequence generation {16a}

This will be a randomized open-label trial. A computer-generated randomization list will be pre-defined. Only the central pharmacist will have access to the randomization list.

##### Concealment mechanism {16b}

Each random number and corresponding treatment will be sealed in an opaque envelope which will only be opened by CHW after enrolment of the participant.

##### Implementation {16c}

The central pharmacist of IRSS-DRCO will generate the allocation sequence. Participants will be enrolled by community health workers who will also assign participants to interventions after confirmation of all eligibility criteria.

#### Assignment of interventions: Blinding

##### Who will be blinded {17a}

Not applicable as the study is an open-label trial.

##### Procedure for unblinding if needed {17b}

Not applicable as the study is an open-label trial.

### Data collection and management

#### Plans for assessment and collection of outcomes {18a}

Data collection and measurement of study parameters will be performed according the developed standard operating procedures. Axillary temperature will be determined using an electronic clinical thermometer. Mid-upper arm circumference (MUAC) will be measured at the mid-point between the tip of the shoulder and the tip of the elbow. Height will be measured using an appropriate Rolla-meter and recorded in centimetres. Weight will be measured using a baby scale for children aged 6 months to 2 years old, and a children’s sitting/standing scale for children over 2 years old. Blood will be collected by finger prick for haemoglobin (Hb) measurement, malaria rapid diagnostic test (RDT), microscopy, and on filter paper for later PCR analyses. A HemoCue® 201^+^ will be used for photometric measurement of Hb in the field following the manufacturer’s procedure. Thick and thin blood films will be stained with Giemsa 3% for 30 min and examined with light microscope. A slide will be declared negative if the examination of 100 thick-film fields does not reveal the presence of asexual parasites. PCR analyses concern a genotyping of amodiaquine resistance molecular markers (*pfcrt* and *pfmdr1*), sulfadoxine resistance marker (*pfdhps*), and pyrimethamine resistance marker (*pfdhfr*) on malaria-positive samples following previously published protocols.

#### Plans to promote participant retention and complete follow-up {18b}

For studies with such a long follow-up period (12 months), loss to follow-up is an important issue. Therefore, by relying on Nanoro health and demographic surveillance system (HDSS), this risk is highly minimized. In addition, 20% corrective measure was allocated to this risk in the sample size calculation to prevent it from affecting the study validity. The supplements that will be used in this study (Plumpy’Doz and zinc) are well known by the population in the management of malnutrition. However, this study will insist on communication with the community/parent/guardians before enrolment in order to improve knowledge and awareness of study product as well as the purpose of the study.

#### Data management {19}

Appropriate individual case record forms (CRFs) will be developed for each participant. Data will be double entered by two independent data clerks in a REDCAP database. Adequate procedures will be put in place to ensure accuracy, reliability, and consistency of records. Control systems will be set-up to independently record the date and time of operator entries and actions that create, modify, or delete records. All the data will be backed up and archived daily.

#### Confidentiality {27}

The medical records of the participants and information collected during this study that display their names or address details will be kept confidential at the IRSS/CRUN. This identifying information will be seen by the ethics committee for health research, or the regulatory authority (both in Burkina Faso) who gives us permission to conduct the study and make sure the study is run properly.

#### Plans for collection, laboratory evaluation, and storage of biological specimens for genetic or molecular analysis in this trial/future use {33}

Dried blood spots will be put into plastic bags and stored at room temperature. Future investigations will only focus on the understanding of the parasite resistance mechanisms. No genetic testing about human host will be performed.

### Statistical methods

#### Statistical methods for primary and secondary outcomes {20a}

Data analysis will be performed using R software package [21] or STATA 14.1 software. A statistical analysis plan will be developed within 6 months of the study commencement. In case of protocol amendment or any unexpected events affecting this plan, it may be revised during the course of the study accordingly. A final statistical analysis plan will be produced before the database lock.

#### Interim analyses {21b}

Not planned yet

#### Methods for additional analyses (e.g. subgroup analyses) {20b}

Not planned yet

#### Methods in analysis to handle protocol non-adherence and any statistical methods to handle missing data {20c}

Analysis population relating to protocol non-adherence and statistical methods to handle missing data will be defined in the statistical analysis plan that will be developed prior to database lock.

#### Plans to give access to the full protocol, participant level-data, and statistical code {31c}

Prior to the start of the study, the protocol will be registered in an international registry and published in an open access journal. The datasets analysed during the current study will be available from the corresponding author on reasonable request.

### Oversight and monitoring

#### Composition of the coordinating centre and trial steering committee {5d}

Prior to the study start, a trial steering committee will be set. This committee will include five independent members: a paediatrician, a nutritionist, a member of the Nanoro health district executive team, and representatives of the national malaria and nutrition programmes (one from each programme). The committee will monitor the evolution of the trial through regular teleconferences and physical meetings (twice during the course of the intervention) and advice on the scientific credibility and on specific issues that may arise during the course of the study. All decisions taken by this committee will be made by majority vote and will be documented.

#### Composition of the data monitoring committee, its role, and reporting structure {21a}

IRSS will contract a freelance monitor to ensure that the study is adequately monitored. The monitor will verify the best conduct of the study through phone calls with the principal investigator and other study staff. Two monitoring visits are planned: an initiation visit before the enrolment of the first participant and a close-out visit after the last patient has completed the follow-up.

#### Adverse event reporting and harms {22}

All the medical products that will be administered in this study are already used as part of either routine management or prevention of malnutrition in Burkina Faso. Therefore, it is anticipated that the study drugs will be well tolerated. However, an efficient pharmacovigilance system will be put in place to ensure prompt reporting and management of adverse events requiring medical care.

#### Frequency and plans for auditing trial conduct {23}

The study protocol is reviewed by technical committee for the examination of authorization for clinical trial requests of the national agency for pharmaceutical regulation which is the regulatory authority in Burkina Faso. An approval was obtained and the study could be subject to audit by this regulatory authority of Burkina Faso anytime if necessary.

#### Plans for communicating important protocol amendments to relevant parties (e.g. trial participants, ethical committees) {25}

Any protocol amendment will be reported to the ethical committee for health research of Burkina Faso and to the national agency for pharmaceutical regulation in Burkina Faso.

#### Dissemination plans {31a}

Dissemination of the study findings is planned not only through scientific papers and conference attendance, but also through meetings with various audiences of interest, including key stakeholders such as decision-makers and public health authorities, health workers, and local community.

## Discussion

Despite the implementation of multiple control strategies, the burden of malaria suggests the need of innovative measures either to improve the efficacy of exiting strategies or to complement them. This study will boost the efficacy of SMC intervention, one the largest and reliable malaria control interventions in Sahelian countries. Most importantly, the study will aim to generate evidence on the efficacy of nutritional supplementation to reduce the burden of malnutrition which constitutes a huge threat in sub-Sahara Africa. Thus, this study will provide critical information for policy-makers and will contribute towards the achievement of SDG 3.

The study will promote economic development and welfare in Burkina Faso. The outcomes of this project will indirectly contribute to the economic development by reducing the burden of malaria and malnutrition, which constitute significant threats to economic development in the country. As well as the wider economic threats, these issues have huge impact at the individual and community levels through reduced attendance in education, reduced working days lost due to disease, reduced household and community incomes, and increased burden on patients because of treatment costs. The combined intervention will also contribute to saving resources for the national malaria and nutrition programmes. This includes time, personnel, logistics allocated for the implementation of SMC, and nutrition prevention strategies.

This study will serve as a pilot of integrated strategies in order to federate resources for better impact. The proposed project will greatly contribute to guide national policy of two distinct entities of the Ministry of Health in their decision-making by providing evidence of the impact of an easily scalable combined intervention, i.e. the National Malaria Control Program and the National Nutrition Direction.

Finally, by relying on existing strategies, the policy implementation of this joint intervention demonstrates its public health sustainability and will be scalable at country and regional levels especially in other Sahel countries sharing similar malaria and malnutrition profile.

### Trial status

This is version 02, 01/05/2020 of the protocol. Ethical and regulatory authority approvals are obtained. Study staff are recruited and trained. At the time of submission, the recruitment of study participants began in July 13, 2020 and was expected to be completed 2 weeks later, i.e. in August 2020. Participants will be followed-up until June 2021. The trial is ongoing. The results of the study are expected in March 2022.

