#### Outcomes {12}

Primary outcomes include (i) the relative incidence of clinical malaria, severe malaria, and anaemia in SMC + vitamin A group (control group) compared to each of the two intervention arms, i.e. SMC + vitamin A + supplement and (ii) the mid-upper arm circumference gain and weight gain from the enrolment to the end of the 12-month study period in the intervention groups compared to the control group. Secondary outcomes include (i) the prevalence of mutant alleles of *pfcrt, pfmdr1, pfdhfr*, and *pfdhps* from the enrolment to the end of the 6-month study period in malaria-positive sample and (ii) SMC coverage in the area which will be determined as the ratio of children who actually received the intervention to the predetermined sample of eligible children from the HDSS dataset. (iii) Compliance will be determined by calculating, for each participant, the ratio between the number of tablets/packets taken and the number of tablets/packets that the patient should have taken. Two groups of participants will be described: compliant = 100% treatment compliance and non-compliant = other cases, and (iv) the incidence of adverse events in each study arms.

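### The stated end of follow-up (June 2021) falls before any child enrolled from 13 July 2020 reaches 12 months, contradicting the 12-month MUAC and weight-gain outcome and the M12 close-out visit

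*Protocol article*

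**What the plan says.** The calendar is given in the Trial status section of the protocol article: "the recruitment of study participants began in July 13, 2020", recruitment "was expected to be completed 2 weeks later, i.e. in August 2020", and "Participants will be followed-up until June 2021". This is the only end date for follow-up in the article.

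The length of follow-up is set elsewhere, and consistently:

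- Participant timeline {13}: "Eligible children will be followed-up for 1 year", with monthly active surveillance for the first 6 months and passive surveillance after that. The Abstract also gives 1 year.
- Outcomes {12}: the second primary outcome is "the mid-upper arm circumference gain and weight gain from the enrolment to the end of the 12-month study period".
- The schedule table under Participant timeline {13} labels the last visit M12 (close-out) and marks weight, height, MUAC and haemoglobin there. The M7–M11 column is empty for every assessment.
- Plans to promote participant retention {18b}: "For studies with such a long follow-up period (12 months), loss to follow-up is an important issue".

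**The concern.** A child's 12-month date is fixed by the enrolment date. If the first enrolment was on 13 July 2020, nobody reaches 12 months before 13 July 2021, so a follow-up that closes in June 2021 closes before the horizon of a primary outcome.

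What is at stake is the timing of the MUAC and weight-gain outcome. Closing in June as written would measure a gain labelled as 12-month at about 11 months. The schedule has no visit between M6 and M12 to stand in for it. The interval would also vary between children, because each child's follow-up would depend on how late that child was enrolled.

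**Working it through.** **Inputs, all from the protocol article**

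- First enrolment: 13 July 2020 (Trial status).
- Last enrolment: two weeks later, but also given as August 2020 (Trial status). 13 July + 14 days = 27 July 2020, so these two descriptions disagree. I use 27 July as the two-week reading, and 1 and 31 August as the limits of the August reading.
- End of follow-up: June 2021, with no day given (Trial status). I take 30 June, the reading most favourable to the plan, and 1 June as the other limit.
- Required follow-up: 12 months from enrolment (Outcomes {12}, Participant timeline {13}). For every enrolment date used here this is 365 days.

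**Formulas**

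- Days available = end of follow-up − enrolment date.
- Shortfall = 365 − days available.
- Months = days ÷ 30.4375.

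**Close on 30 June 2021**

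| Enrolled | 12 months due | Days available | Months | Shortfall (days) |
|---|---|---|---|---|
| 13 July 2020 | 13 July 2021 | 352 | 11.56 | 13 |
| 27 July 2020 | 27 July 2021 | 338 | 11.10 | 27 |
| 1 August 2020 | 1 August 2021 | 333 | 10.94 | 32 |
| 31 August 2020 | 31 August 2021 | 303 | 9.95 | 62 |

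**Close on 1 June 2021**

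| Enrolled | Days available | Months | Shortfall (days) |
|---|---|---|---|
| 13 July 2020 | 323 | 10.61 | 42 |
| 27 July 2020 | 309 | 10.15 | 56 |
| 1 August 2020 | 304 | 9.99 | 61 |
| 31 August 2020 | 274 | 9.00 | 91 |

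**Reading the result.** The plan's figure of 12 months is not reproduced for any enrolment date on or after 13 July 2020. With two-week recruitment and a close on 30 June, the shortfall is 13 to 27 days. A close at the start of June, or recruitment to the end of August, takes the largest shortfall to about two months (56 or 62 days). Both together give 91 days, the outer limit of what the text allows.

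**Could M12 mean the twelfth calendar month?** If July 2020 counted as month 1, June 2021 would be month 12. The schedule, however, has a separate time 0 for allocation before M1, and both Outcomes {12} and Participant timeline {13} count a full year from enrolment or inclusion. That reading does not remove the conflict.

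**The case against.** The strongest reply is that Trial status is a short journal note, while the design sections all agree on 12 months. Nothing says that visits stop on 30 June whatever a child's enrolment date. The sentence before it is also loose about dates, since two weeks after 13 July is not August. The likeliest explanation is a calendar slip, with M12 visits intended for July or August 2021. This is fair, and it limits the severity. It does not remove the contradiction: the note gives the only end date in the article, and it was written prospectively while the trial was running.

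It is also right that the damage would be limited. Allocation is randomised 1:1:1 and one calendar applies to all arms, so an early close would shorten follow-up alike in each arm and gives no evident reason for bias between them. The malaria outcome is little affected, because active surveillance in the first 6 months is meant to cover the transmission peak and the sample size rests on a rainy-season proportion.

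A reader might infer more than the documents support:

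- *That the 12-month outcomes cannot be obtained at all.* A June close-out visit would still measure MUAC and weight, only early.
- *That incidence rates would be understated.* This needs a fixed 12-month denominator, which the article never states. The primary outcome is a relative incidence, in which an error common to the arms would largely cancel.
- *That the resistance-marker outcome suffers.* Outcomes {12} ends that outcome at 6 months.
- *That the M12 visit must precede the 2021 SMC round.* The article gives no 2021 SMC date. Children enter after the first SMC dose of the first round, so enrolment plus 12 months may fall at or after the next season's first round.

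**Conclusion.** The contradiction stands on the article's own dates and needs no outside figure. If follow-up closes in June 2021 as written, no child completes 12 months, and the MUAC and weight-gain outcome is measured about 2 to 4 weeks early under two-week recruitment and a 30 June close. The gap grows to about 2 months if recruitment ran through August or the close came at the start of June. It is the same in all arms, so it affects the definition and labelling of the outcome and the absolute gains more than the comparison between arms.

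The size rests on two assumptions that the text leaves open: the day in June on which follow-up closes, and whether recruitment ended on 27 July or in August. The conclusion that nobody reaches 12 months depends on neither. This should be fixed. It is more than clerical because it concerns the assessment time of a primary outcome with no fallback visit after M6, but it does not threaten the trial's validity.

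**What to change.** Reconcile Trial status with Outcomes {12}, Participant timeline {13}, the schedule table and the retention section {18b}, in one of two ways:

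1. State the end of follow-up as each child's own enrolment date plus 12 months, running from 13 July 2021 to 27 July 2021 on two-week recruitment, or into August 2021 if enrolment ran into August 2020. The 12-month definitions then stand.
2. If follow-up does close in June 2021, restate the horizon of the MUAC and weight-gain outcome and the name of the close-out visit, wherever they appear, as the follow-up actually achieved (about 11 months).

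In either case, compute incidence on each child's actual person-time. Also correct the recruitment sentence: give either 27 July 2020 or the actual August date as the end of recruitment.

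The first option costs 13 to 27 days of passive follow-up beyond 30 June 2021 on two-week recruitment, and up to 62 days for a child enrolled on 31 August. The second is a change of wording. Neither adds a visit.
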